## Abstract

**Background:**

Acute trauma of the wrist is one of the most frequent reasons for visiting the Emergency Department. These patients are routinely referred for radiological examination. Most X-rays however, do not reveal any fractures. A clinical decision rule determining the need for X-rays in patients with acute wrist trauma may help to percolate and select patients with fractures.

**Methods/Design:**

This study will be a multi-center observational diagnostic study in which the data will be collected cross-sectionally. The study population will consist of all consecutive adult patients (≥18 years) presenting with acute wrist trauma at the Emergency Department in the participating hospitals.

This research comprises two components: one study will be conducted to determine which clinical parameters are predictive for the presence of a distal radius fracture in adult patients presenting to the Emergency Department following acute wrist trauma. These clinical parameters are defined by trauma-mechanism, physical examination, and functional testing. This data will be collected in two of the three participating hospitals and will be assessed by using logistic regression modelling to estimate the regression coefficients after which a reduced model will be created by means of a log likelihood ratio test. The accuracy of the model will be estimated by a goodness of fit test and an ROC curve. The final model will be validated internally through bootstrapping and by shrinking it, an adjusted model will be generated.

In the second component of this study, the developed prediction model will be validated in a new dataset consisting of a population of patients from the third hospital. If necessary, the model will be calibrated using the data from the validation study.

**Discussion:**

Wrist trauma is frequently encountered at the Emergency Department. However, to this date, no decision rule regarding this type of trauma has been created. Ideally, radiographs are obtained of all patients entering one of the participating hospitals with trauma to the wrist. However, this is ethically and logistically not feasible and one could argue that patients, for whom no radiography is required according to their physician, are not suspected of having a distal radius fracture and thus are not part of the domain.

**Trial registration:**

This study is registered at the Netherlands Trial Register (NTR 2544) and was granted permission by the Medical Ethical Committee of the Academic Medical Center Amsterdam on 06-01-2011.

## Background

An acute trauma of the wrist is one of the most frequent reasons for visiting the Emergency Department, and fractures of the distal radius account for an estimated 17% of all fractures diagnosed [1,2]. The incidence of distal radius fractures was recently reported by Swedish researchers at an incidence of 26% per 10,000 person-years [3]. There are indications that in patients with wrist trauma most radiological examinations performed are redundant, resulting in unnecessary radiation exposure for the patient, as well as increased waiting times and a waste of resources [4]. The percentage of radiographs which reveal a distal radius fracture has been determined in a separate retrospective study conducted by our research group in the three Dutch hospitals that participate in the current study. In 2010, seventeen hundred and forty-two patients who were suspected of having a fracture were sent for X-ray series of the distal radius or carpus. Of all X-ray series which were performed on these patients, 50% did not show a fracture.

A clinical guideline concerning the X-ray referral policy may help to select and percolate patients with fractures. In 1987, Gleadhill et al. already concluded that: Clinical guidelines on selecting patients for radiography for certain injuries and emergencies reduced the overall X ray referral rate by 18,5% [5].

In 1991, Stiell et al. conducted a study which showed that the vast majority of ankle trauma patients was radiographically examined upon presentation [4]. They established that only 4.3% of these patients were found to have significant midfoot fractures and 9.3% were diagnosed with significant malleolar fractures. Subsequently the authors developed the renowned Ottawa Ankle Rules. After implementation of this clinical decision rule, a relative reduction (RR) of 28% of ankle radiography was recorded in the intervention hospital, whilst the control site showed a 2% increase. A reduction of time spent in the Emergency Department (116 minutes vs. 80 minutes) was also found without any missed fractures or patient discontent [6]. Bachmann et al. even reported a 30-40% reduction of unnecessary radiographs in their systematic review of all literature on the accuracy of the Ottawa Ankle Rules [7].

In 2003, Cevik et al. evaluated the value of physical findings to predict fractures in patients with acute wrist trauma [8]. They included fifty-five patients in their study and concluded that edema, pain on grip and supination, pain on active and passive motion and localized tenderness can be valuable to predict a fracture.

Recently, Calco-Lorenzo et al. analyzed the possibility of creating a clinical decision rule for the assessment of conventional X-rays in acute wrist trauma [9]. They employed 46 different anamnestic and examination variables and included 179 patients in their study. They concluded that an age equal or higher than thirty-five, edema in the dorsum of the wrist, limited supination or radial deviation as compared to the contralateral wrist and pain on performing the distal radioulnar drawer test, was predictive of the presence of a distal radius fracture. However, they advised "a broader study should be undertaken to assess the feasibility of introducing a clinical decision rule".

Therefore, the primary aim of this study is to formulate a clinical decision rule to determine when an X-ray of the distal radius is necessary in patients presenting to the Emergency Department following wrist trauma.

The second aim of this study is to validate this decision rule in a new patient population and to present it as simplified risk score.

## Methods/Design

This study consists of two components in which the data will be collected cross-sectionally. The data will be collected in three different hospitals during a period of six months. The participating hospitals include one university hospital, one non-academic teaching hospital, and one non-teaching hospital.

One component of this research comprises a study which will be performed to determine which combination of clinical parameters has a predictive value for the presence of a distal radius fracture in adult patients presenting to the Emergency Department following acute wrist trauma. This will be done by creating a model from the data collected in the university hospital and the non-academic teaching hospital. This model will be internally validated by bootstrapping. In the second component of this study, the developed prediction model will be validated in a new dataset. This dataset will be collected simultaneously in the third hospital, the non- teaching hospital, using the same approach as in the other hospitals.

### Study population

The study population is defined as all consecutive adult patients presenting at the Emergency Departments in the participating hospitals following wrist trauma and who are suspected to have sustained a distal radius fracture. Patients are suspected of having sustained a distal radius fracture when pain on pressure in the wrist area is indicated. The wrist is defined as the proximal segment of the hand consisting of the carpal bones and the associated soft parts and the distal segment of the ulnar and radial bone. A traumatic wrist injury is defined as a high or low energetic accident involving the wrist, e.g. a fall on the outstretched hand or a motor vehicle accident.

#### Inclusion criteria

• Patient aged 18 years and older

• An acute trauma of the wrist (< 72 hrs following trauma)

• Pain on pressure in wrist area

#### Exclusion criteria

• Pre-existent neurological pathology in the affected limb

• Previous fracture of distal radius <3 months

• Patients referred from another hospital where X-rays of the wrist were performed

• Multi trauma patient

• Patients who are not considered to be competent or capable by their treating physician to answer any questions regarding pain or mechanism of trauma as listed on the Case Report Form (Additional file 1).

#### Sample size

Due to the multivariable character of this study, a sample size calculation is not applicable, and we will therefore use a convenience sample. A common guideline is that the number of potential determinants should not exceed 10% of the number of events, in this case distal radius fractures. The Case Report Form (CRF, additional file 1) lists 20 parameters, therefore requiring a minimum of 200 patients with a distal radius fracture (see appendix). In preparation of this study, we recently conducted a retrospective study in the participating hospitals to determine the number of X-rays performed for wrist trauma. In the academic hospital, it was found that 550 radiographs in patients with acute wrist trauma were performed during a one year period. In the non-academic teaching hospital, this figure was even higher: 2300 in one year. The percentage of radiographs which reveal a distal radius fracture is currently being determined in a separate study performed at these hospitals and is estimated to be about 50%. We expect that a period of six months will suffice to include enough patients (500) to formulate the decision rule. No strict guidelines for the required sample size of external validation studies exist. However, we aim to perform this analysis in a dataset which is of equal size as the development data set. Therefore, to validate the decision rule in a new population, this data will be collected simultaneously in the third hospital, the non-teaching hospital, using the same approach as in the other two hospitals.

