### Study procedures

Data collection will take place from February 2011 till August 2011. During this period, patients presenting following an acute traumatic injury of the wrist will receive care as usual. The difference is that, upon presentation with wrist pain following trauma, an additional Case Report Form (CRF) containing multiple clinical parameters will be completed by the treating physician. These clinical parameters are defined by trauma-mechanism, physical examination and functional testing and include; mechanism of trauma; swelling of the distal radius, swelling of the Anatomical Snuffbox; visible deformity of the wrist; palpability of radial artery pulsations; pain on palpation of the distal radius, distal ulna, Anatomical Snuffbox, radial styloid, ulnar syloid and Lister's tubercle; pain on dorsal flexion, palmar flexion, supination, pronation ulnar deviation, radial deviation; difference in prehensile strength test between affected and unaffected side; outcome distal radial drawer test and pain on axial compression (see appendix). Radiographs of the distal radius will be performed according to Dutch guidelines; at least one posterior anterior (PA) and one lateral view with the elbow in 24 degrees of flexion. Additional imaging for injuries associated with wrist trauma, e.g. suspected fracture of the scaphoid, can be performed selectively and will be on account of the treating physician. The independent radiologist assessing the outcome using the reference standard (X-rays) will be blinded from the results of the CRF to prevent incorporation bias. The dichotomous nature (yes/no) of the CRF and the fact that it is a standardized way of history taking and examination, will decrease interobserver variability and thus minimize underestimation of the potential diagnostic value of the parameters.

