Upon completion of the data collection in all three participating medical centers, a prediction rule will be developed based on data from two of the participating hospitals; the academic hospital and the non-academic teaching hospital. Since prediction rules always perform perfectly in the patient population they were generated from, a validation study in a new study population is required to assess its predictive quality. To ensure the most stringent form of validation, the rule will be validated in data from the third hospital, the non-teaching hospital. This method is also known as domain validation. The method of data collection in the third hospital will be similar and done simultaneously. This dataset will be comparable to the first regarding size and informative parameters and the model will be tested to verify its predictive value of the primary outcome: distal radius fracture. If necessary, the model will be updated and finally it will be presented as a simplified risk score.

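### At the 2010 patient count, six months in the three hospitals yields about 871 X-rayed patients, not the roughly 1000 implied by 500 for development plus an equal-sized validation set

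*Protocol article*

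**What the plan says.** Under Sample size, the Protocol article declines a formal calculation and calls the sample a convenience sample. It applies a rule of ten fractures per candidate parameter: 20 parameters, hence at least 200 distal radius fractures. It gives 550 radiographs a year in the academic hospital and adds: "In the non-academic teaching hospital, this figure was even higher: 2300 in one year". With about half of radiographs expected to show a fracture, it concludes: "We expect that a period of six months will suffice to include enough patients (500) to formulate the decision rule".

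For external validation the same section says "we aim to perform this analysis in a dataset which is of equal size as the development data set", with the data coming only from the third, non-teaching hospital over the same period. Study procedures repeats this without qualification: "This dataset will be comparable to the first regarding size and informative parameters".

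The Background gives a count in patients, from a retrospective study by the same group: "In 2010, seventeen hundred and forty-two patients who were suspected of having a fracture were sent for X-ray series of the distal radius or carpus". The sentence before it places that study "in the three Dutch hospitals that participate in the current study", so the count covers all three sites.

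On duration, Methods/Design says "The data will be collected in three different hospitals during a period of six months", and Study procedures says "Data collection will take place from February 2011 till August 2011".

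**The concern.** Two volume figures are given for the same hospitals, and they do not fit together. The two development hospitals are credited with more radiographs a year than the Background credits patients to all three hospitals. Sample size then moves from radiographs to an expected number of patients with no conversion. Once accrual is counted in patients, the total available in six months falls below the sum of the two stated set sizes.

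The validation set is the more exposed. It must come wholly from a hospital for which the article gives no volume. The rule is meant to identify patients who can go without an X-ray, so the key external result is its sensitivity, and the precision of that estimate depends on the number of fractures in the validation set.

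**Working it through.** **Inputs from the Protocol article**
- 20 parameters, 200 fractures minimum, about 50% fractures, 500 development patients, validation set of equal size, 550 and 2300 radiographs a year (Sample size).
- 1742 X-rayed patients in 2010, three hospitals (Background). I take this as a full calendar year.
- Six months (Methods/Design); February till August 2011, and at least two views per examination (Study procedures).
- Outcome known only for patients sent for X-ray (Discussion), so X-rayed patients are the ceiling on analysable patients.

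**1. The plan's own figure.** 20 × 10 = 200 fractures, which reproduces. At 50%, 200 / 0.50 = 400 patients. The stated 500 is not derived in the text, but it would give 500 × 0.50 = 250 fractures and so satisfies the minimum.

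**2. Accrual in patients.** 1742 × 6/12 = 871. Against 500 + 500 = 1000 the gap is 129, or 12.9%. Reaching 1000 at this rate takes 1000 / (1742/12) = 6.9 months before exclusions.

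**3. Seven-month reading of the dates.** 1742 × 7/12 = 1016. This falls below 1000 once exclusions exceed 1 − 1000/1016.2 = 1.6%.

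**4. The two volume figures.** 550 + 2300 = 2850 radiographs a year in two hospitals, against 1742 patients in three. If year and population are the same, there must be at least 2850/1742 = 1.64 radiographs per patient, and that bound leaves no patients for the third hospital.

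**5. Implied split.** The number of radiographs per patient, r, is not stated, so I assume a range. Six-month development patients = 2850/(2r); third hospital = 871 − 2850/(2r).

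| r (assumed) | Development | Third hospital |
|---|---|---|
| 2 | 712.5 | 158.5 |
| 3 | 475 | 396 |
| 4 | 356 | 515 |

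No r gives 500 in both, because the total is 871. Development alone reaches 500 if its two hospitals supply at least 500/871 = 57% of the total.

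**6. The 200-fracture minimum in both sets.** This needs 2 × 400 = 800 patients, below 871. It therefore requires a near-even split and exclusions no greater than 1 − 800/871 = 8.2%. An exactly even split gives 435.5 patients and about 218 fractures per set before exclusions.

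**7. Precision of sensitivity, for illustration.** With r = 2, the third hospital has about 158 × 0.5 = 79 fractures; 77/79 detected (97.5%) has an exact (Clopper–Pearson) 95% CI of 91.2–99.7%. With 250 fractures, 245/250 (98.0%) gives 95.4–99.3%. The observed proportions differ slightly, so the comparison is approximate.

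**The case against.** The sentence about 500 patients concerns development only, and nothing in the article contradicts it. With two radiographs per patient, the two hospitals would supply about 712. That stands.

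The only firm requirement is 200 fractures. Equal validation size is introduced as an aim, after the remark that no strict guidelines exist. Two sets of 400 fit within 871. This also stands, though the margin is thin, and Study procedures states comparable size as a fact rather than an aim.

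A reader might infer that the plan requires 500 + 500 and that this is impossible. The documents do not support that. The 871 assumes that 1742 covers a full year and that the 2010 rate holds in 2011. A seven-month window would just exceed 1000 before exclusions. What can be said is that both sizes are not expected at the 2010 rate in six months. The 871 is also likely to be generous: the Background mentions none of the age, 72-hour, multi-trauma or competence restrictions that this study applies.

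A reader might also infer that the 2850 must be single films. That is likely but not shown. The radiograph counts name no year, and the two sources may define cases differently. Either way, they cannot serve as patient counts unconverted.

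Finally, the 79-fracture case is one assumed split; at four radiographs per patient the third hospital would reach 515. It illustrates what is at stake and does not forecast the validation set.

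**Conclusion.** The point holds as a conflict between the stated sizes and the article's own patient count. The expected six-month total is about 871 against about 1000, 13% short before exclusions, given a full-year 2010 count, a stable rate and a six-month window. The radiograph counts offered as the feasibility basis exceed the three-hospital patient count and need reconciling with it. The claim that the validation set will match the development set rests on no stated volume for the hospital that must supply it. The 500 for development remains feasible on its own, and the 200-fracture minimum can be met in both sets only under the narrow conditions in step 6.

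**What to change.** - Reconcile Background and Sample size in one unit, patients, and say what the 550 and 2300 count, for which year and in which population.
- From the retrospective data, restate the expected eligible patients and distal radius fractures for the development set and for the third hospital over the collection period. State whether that period is six or seven months.
- In Sample size and Study procedures, replace equal or comparable size with the validation size that the third hospital's count supports, and give the expected 95% CI for sensitivity at that number of fractures.

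The cost is a re-tabulation of data from a study the group has already carried out, assuming these can be broken down by hospital and by this study's criteria, and rewording of a few sentences. The downside is that the stated sizes will probably look less favourable.

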## Outcome measurements

### Main study parameter/endpoint

The main study endpoint is a distal radius fracture as assessed by a blinded and independent skeletal radiologist on conventional X-rays series; one posterior anterior (PA) and one lateral view with the elbow in 24 degrees of flexion. A fracture is defined as the presence or disruption of one or more of the cortices of the distal radius. Malalignment in the distal radial ulnar joint and radial carpal joint is regarded as a potential fracture. Small avulsions at bony attachments sides of ligaments are considered to be a fracture as well.

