### Statistical analysis

The data from the academic hospital and the non-academic teaching hospital will be used to develop the model. The data will be assessed by using a multivariable analysis. However, to prevent too optimistic estimates of the accuracy of the diagnostic model, a more liberal p-value for statistical significance will be employed (p = 0.15). Logistic regression modeling will be used to estimate the regression coefficients and thus the log odds of a fracture versus no fracture after which a reduced model will be created by means of a log likelihood ratio test.

The accuracy of the model will be estimated by a goodness of fit test and a ROC curve. If applicable, different models can be compared using the tests mentioned above. The final model will be validated internally through bootstrapping to estimate overfitting in the calibration and discrimination stated above. By averaging the optimism an adjusted model will be generated.

Henceforth, the prediction rule will be validated in a new data set, which will be collected simultaneously in the third hospital; the non-teaching hospital. If necessary, the model will be updated using the data from the validation study, by adjusting the intercept.

Finally, the prediction model will be presented as a simplified risk score which can be used by physicians to determine the need for an X-ray in patients presenting with wrist trauma at the Emergency Department.

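### The outcome is distal radius fracture only, but enrolment covers the whole wrist and the score's stated use is not limited to distal radius radiographs

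*Protocol article*

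**What the plan says.** - **Outcome.** Under Main study parameter/endpoint: "The main study endpoint is a distal radius fracture as assessed by a blinded and independent skeletal radiologist on conventional X-rays series". The definition that follows is tied to one bone: "A fracture is defined as the presence or disruption of one or more of the cortices of the distal radius". Two extensions come next. Malalignment at the distal radioulnar or radiocarpal joint is treated as a potential fracture, and "Small avulsions at bony attachments sides of ligaments are considered to be a fracture as well". No bone is named for the avulsions. Study procedures repeats distal radius fracture as the primary outcome.
- **Coding.** Under Statistical analysis, the logistic model estimates "the log odds of a fracture versus no fracture".
- **Who is enrolled.** Study population defines the wrist as the carpus with its soft tissues plus the distal ulna and distal radius. Suspicion of a distal radius fracture is itself defined as tenderness on pressing that area, and the Inclusion criteria ask for the same. The Exclusion criteria do not remove patients with carpal or ulnar fractures.
- **Purpose, narrow.** The primary aim, in the Background, is a rule "to determine when an X-ray of the distal radius is necessary in patients presenting to the Emergency Department following wrist trauma".
- **Purpose, wide.** The Statistical analysis section closes by offering the risk score to physicians "to determine the need for an X-ray in patients presenting with wrist trauma at the Emergency Department". The abstract's background is similarly open: "A clinical decision rule determining the need for X-rays in patients with acute wrist trauma may help to percolate and select patients with fractures".
- **Other imaging.** Study procedures leaves further imaging for associated injuries, with the scaphoid as the example, to the treating physician.

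**The concern.** Three scopes should agree and do not: the patients who enter, the event that is modelled, and the decision the score is meant to serve. A patient with an isolated scaphoid, other carpal or distal ulnar fracture qualifies for the study but is a non-event in the model. If that patient's score is low, the classification counts as correct.

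That is harmless if the score decides only whether the distal radius needs a radiograph and everyone reads it so. It is not harmless if a low score is taken to mean that no radiograph is needed after wrist trauma, as the closing sentence of Statistical analysis allows. On that use the relevant error is any missed wrist fracture, and none of the planned measures (goodness of fit, ROC curve, bootstrap correction, external validation) would show it, because all are computed against the radius-only outcome. The stake is a patient-safety claim resting on evidence that does not address it.

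**Working it through.** **Step 1. The texts side by side**

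| Element | Scope | Section |
|---|---|---|
| Entry | Whole wrist | Study population; Inclusion criteria |
| Event | Distal radius, with unclear extensions | Main study parameter/endpoint |
| Primary aim | Radiograph of the distal radius | Background |
| Use of the final score | Radiograph after wrist trauma, no bone named | Statistical analysis |

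The event matches the primary aim. It does not match the stated use or the entry criteria.

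**Step 2. The plan's own figure**

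Sample size allows candidate parameters up to 10% of the number of events and lists 20 of them: 20 / 0.10 = 200 distal radius fractures. This reproduces the stated minimum. With 500 patients and about 50% distal radius fracture, 500 × 0.50 = 250 events, or 250 / 20 = 12.5 per parameter. That leaves 500 − 250 = 250 non-events. The concern does not depend on these figures; they only give a base for the illustration.

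**Step 3. Illustration of size**

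The documents give no rate of carpal or ulnar fracture without distal radius fracture. Assumptions:

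- a share *s* of the 250 non-events, between 5% and 30%, has another wrist fracture;
- sensitivity for distal radius fracture is 100%;
- specificity is 50%, so 250 × 0.50 = 125 non-events score low;
- scoring low is unrelated to having another fracture;
- none of these other fractures is captured by the avulsion or malalignment wording.

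Other fractures = 250*s*. Those scoring low = 250*s* × 0.50. Sensitivity for any wrist fracture = (250 + 250*s* × 0.50) / (250 + 250*s*).

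| *s* | Other fractures | Of these, low score | Sensitivity, any wrist fracture |
|---|---|---|---|
| 5% | 12.5 | 6.25 | 256.25 / 262.5 = 97.6% |
| 10% | 25 | 12.5 | 262.5 / 275 = 95.5% |
| 20% | 50 | 25 | 275 / 300 = 91.7% |
| 30% | 75 | 37.5 | 287.5 / 325 = 88.5% |

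With specificity at 30%, the low-score fractures are 3.75, 7.5, 15 and 22.5, and sensitivity is 98.6%, 97.3%, 95.0% and 93.1%. In every row the reported sensitivity for distal radius fracture is 100%. Under these assumptions the share of low-score non-events with another fracture equals *s*, whatever the specificity.

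**Step 4. Does the documents' 50% settle *s*?**

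No. Sample size gives about 50% as the share of radiographs showing a distal radius fracture. The Background introduces its retrospective figure in the same terms, but then reports that half of the series of the radius or carpus showed no fracture, without giving the site of the others. If that second 50% means any fracture, some unknown part of it lies outside the radius. The two terms are used as if interchangeable, and *s* cannot be derived from either figure.

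**The case against.** The strongest reply is that choosing one target condition is a legitimate design decision and that most of the article keeps to it: the primary aim, the abstract's methods, the endpoint and Study procedures all name the distal radius. Study procedures also treats scaphoid imaging as a separate decision. The abstract's background sentence only says what a rule might help with. On this view one loose closing sentence is the whole problem.

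Much of that stands, and it rules out several stronger readings that a reader might reach:

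- **That the score is offered for any wrist radiograph.** No section says so. The wide wording is unrestricted, and it conflicts with a restricted primary aim.
- **That missed fractures will be credited as radiographs avoided, so that the saving is overstated.** True-negative coding points that way, but the protocol defines no measure of radiographs avoided.
- **That all non-radius fractures are non-events.** The avulsion sentence names no bone and the malalignment sentence is open, so some non-radius lesions may be counted.
- **That snuffbox signs will take negative weights and steer carpal injuries towards a low score.** Nothing in the documents indicates the sign of those coefficients or whether the items survive model reduction.

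Whether other fractures are already recorded cannot be judged either, because the case report form and full protocol are not shown.

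The reply does not remove the conflict over use. The imaging sentence in Study procedures describes care during data collection; it does not say that a physician holding a low score would still image for carpal or ulnar injury. Describing the population as suspected of distal radius fracture does not narrow it, since that suspicion is defined by tenderness anywhere in the wrist.

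**Conclusion.** The concern holds in a limited form. The modelled outcome is narrower than the enrolled population and narrower than the use stated at the end of Statistical analysis, and that use conflicts with the primary aim in the Background. A low-score patient with only a carpal or ulnar fracture would generally be coded a true negative, so the planned accuracy measures cannot support the unrestricted use. They can support the narrow aim.

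The size is unknown. The 97.6% to 88.5% range shows the direction and how the gap grows with the share of other fractures. It rests on assumed rates and on independence between score and other fracture, and is not a forecast for this study. Because a low score may lead to no imaging, the point deserves correction even though the error is mainly one of stated scope.

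**What to change.** 1. **Reconcile the stated use.** Bring the closing sentence of Statistical analysis, and the abstract's background wording, into line with the primary aim by limiting the claim to radiographs of the distal radius. State that the score is not validated to rule out carpal or ulnar fracture.
2. **Record other fractures.** Have the same blinded reading note any other fracture visible on the series obtained. In both the development and validation sets, report the number and type of these among patients the score classes as low risk. Give sensitivity for any visible wrist fracture, with an exact confidence interval, as a secondary result.
3. **State its limit.** The basic series is a PA and a lateral view and further imaging is selective, so this secondary figure is likely to be incomplete and should be labelled as covering visible fractures only.
4. **Clarify the endpoint.** Say which bones the avulsion wording covers and how a potential fracture from malalignment is coded in the binary outcome.

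The cost is one extra reading field and one table. The primary model and its event requirement do not change because of the added field. The score's stated benefit may look smaller.
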